### Study design

Using a parallel arm design, clinics will be randomly allocated either to receive community-based HIVST distribution in a defined catchment area, or to continue with usual clinic-based HTS (standard of care [SOC]). Clinic catchment areas will be randomized rather than individual testers because the intervention was designed to be delivered by community-based distributors. Individual-level randomization would therefore be inappropriate.

In Malawi, 22 rural primary health clinics will be randomized 1:1 to receive the HIVST intervention or SOC. Within the HIVST intervention arm, CBDAs will also be randomized 1:1 to provide either referrals to home-based ART initiation or the usual referrals to the clinic. Each clinic will contain a pre-defined, concentrated area of implementation, with two villages in each area selected for the baseline and endline household surveys, respectively.

In Zambia, 12 primary health clinics in 4 districts will be pair-matched within districts by distance to the district medical office and catchment area population, and randomized 1:1 to provide the HIVST intervention or SOC.

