#### Zambia

As in Malawi, the survey sample size was calculated to ensure sufficient power to identify a difference in the primary outcome between those receiving the HIVST intervention and those receiving standard care, and uses similar methods. We estimated that the cluster coefficient of variation (k) was 0.2, and that cluster populations were larger than in Malawi. Using 2013–2014 DHS data, baseline rates for adults tested in the last 12 months is estimated to be between 28.6–57.1% (lower in men than women). For this sample calculation, we will assume a testing rate of 50% in the standard of care arm. For a two-sample comparison of matched proportions across 6 pairs of matched communities, we will have 80% power to detect a 50% relative difference in recent HIV testing if we recruit around 400 respondents per community, or 4800 respondents in total.

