### Randomization

The Malawi trial includes two stages of randomization. In the first stage, clinic catchment areas will be allocated to HIVST or standard of care arms using restricted randomization. To ensure that intervention and standard of care clinics are evenly distributed geographically across the study area, we will restrict the number of intervention clinics in each district, with larger districts to include at least 35% intervention clinics. We will balance arms in terms of number of testers, proportion of positive tests, and total catchment population across clinics. The study statistician (MN) provided a list of 1000 eligible randomization combinations to the study team and the final randomization scheme was selected in a public ceremony in Blantyre, Malawi on 21 March 2016.

In the second-stage randomization, we will randomize all CBDAs providing HIVST to home-based initiation of ART or standard of care at a 1:1 ratio. CBDAs will be randomized in blocks of varying sizes from 2 to 12 CBDAs, with the distribution of block sizes following Pascal’s triangle (i.e., 1:5:10:10:5:1).

In Zambia, clinics will be randomized 1:1 within matched pairs to receive the HIVST intervention or standard of care. Randomization was conducted by the statistician (BH) and was completed on 24 June 2016.

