### Trial analysis

All analyses will be completed in Stata 14, on an intention-to-treat basis, and will use methods appropriate for CRTs with a small number of clusters [18]. Reporting will conform to the 2010 CONSORT statement as applicable to cluster randomized trials [22].

Analyses will be conducted separately by country. Initial analyses will compare characteristics of households and respondents across arms at baseline. These baseline analyses will be completed before analysis of endline data begins. Characteristics of households and respondents at endline will be summarized by arm, so that imbalances can be accounted for in our final analysis. Missing data will be examined for each variable and for each cluster or individual participant. A systematic assessment of missingness will be conducted to ascertain the reason and possible mechanism for missing data by identifying the quantity of missing data and patterns within the data. Missingness will be examined by cluster and between randomised arms to assess for systematic biases.

Primary and secondary trial outcomes will be compared using cluster-level unadjusted and adjusted means of recent testing. The analysis will give each cluster equal weight. For the unadjusted analysis, the overall prevalence of the outcome for each cluster will be calculated, and a log transformation will be applied to the prevalence for each cluster if needed. If there are any clusters with no events, one event will be added to all clusters so that the log transformation can be conducted. The mean and standard deviation of the log prevalence will be used to obtain the geometric mean and associated 95% confidence intervals for each trial arm.

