For the adjusted analysis, a two-stage approach will be used. First, a logistic regression model including individual-level adjustment factors but not trial arm will be fitted, and predicted probabilities from this model used to estimate the ratio of observed to expected outcome events for each cluster. This ratio will be log transformed, and a t-test of the difference between logs by arm will be used to estimate the prevalence ratio, 95% confidence interval, and *p*-value. For both unadjusted and adjusted analyses, we will report risk ratios and risk differences. If adjustment for cluster-level factors is considered necessary, this will be conducted at the second stage using linear regression of the log ratio of observed and expected values on arm and cluster level factors, with appropriate adjustment for the degrees of freedom. The adjusted analysis will serve as the primary analysis of each trial. Sensitivity analysis for the primary outcome of recent test for HIV will be carried out by comparing complete case analysis results with those where missing outcome status are re-classified as yes and no.

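### Zambia is randomised within 6 matched pairs and powered on a matched comparison, but the primary test stated for both trials is a by-arm t-test that does not use the pairs

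*Protocol article*

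**What the plan says.** Three places fix the Zambia design as paired.

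- Study design: "12 primary health clinics in 4 districts will be pair-matched within districts by distance to the district medical office and catchment area population".
- Randomization: "In Zambia, clinics will be randomized 1:1 within matched pairs to receive the HIVST intervention or standard of care".
- Power calculations, Zambia: the sample size is set "For a two-sample comparison of matched proportions across 6 pairs of matched communities", with the claim that "we will have 80% power to detect a 50% relative difference in recent HIV testing".

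Table 2 also has a pair column. Malawi, in contrast, uses restricted randomisation of 22 clinics without pairs.

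The Trial analysis section then describes one procedure for both trials. The unadjusted analysis summarises each arm separately: "The mean and standard deviation of the log prevalence will be used to obtain the geometric mean and associated 95% confidence intervals for each trial". In the adjusted analysis, which is declared primary for each trial, log observed/expected ratios are formed per cluster and "a t-test of the difference between logs by arm will be used to estimate the prevalence ratio", its confidence interval and its p-value. A second-stage linear regression on arm and cluster-level factors is allowed if judged necessary. Pair is not named there or anywhere else in the section.

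**The concern.** A by-arm t-test estimates its error from the spread of clusters within each arm. In a pair-matched trial that spread includes differences between pairs, which cancel from the treatment contrast because each pair supplies one clinic to each arm. In Table 2 the pairs do differ in kind. Four are rural (7,673 to 15,694 people, 33 to 90 km from the district medical office). Two are peri-urban (24,078 to 53,249 people, 8 to 9 km). If testing levels follow these differences, the stated test carries variation that the randomisation has already removed.

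At stake are the confidence interval and p-value of the Zambia primary outcome, in a trial of only 12 clusters, and the agreement between the power statement and the test that will be run.

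**Working it through.** **1. Which comparison does the 80% rest on?**

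Inputs from the Zambia power section: p0 = 0.50 ("we will assume a testing rate of 50% in the standard of care arm"), a 50% relative difference so p1 = 0.75, k = 0.2 ("We estimated that the cluster coefficient of variation (k) was 0.2"), n = 400 per community, 6 pairs, 80% power. Alpha 0.05 is stated for Malawi only; I assume it, two-sided, for Zambia, where the methods are said to be similar.

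On the log-ratio scale, which is the scale of the planned test:

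- d = ln 1.5 = 0.4055, so d² = 0.1644
- V = 2k² + (1-p0)/(n·p0) + (1-p1)/(n·p1) = 0.0800 + 0.0025 + 0.0008 = 0.0833
- c = a + (1.960 + 0.842)² × V / d² = a + 7.849 × 0.0833 / 0.1644 = a + 3.98

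The small-sample term a is 2 for a pair-matched design and 1 for an unmatched one.

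| Form | Clusters per arm needed | Power with 6 |
|---|---|---|
| Log scale, matched | 5.98 | 80.2% |
| Log scale, unmatched | 4.98 | 88.1% |
| Proportion scale, matched | 6.22 | 77.9% |
| Proportion scale, unmatched | 5.22 | 86.2% |

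Of these four, only the matched log-scale form returns the stated 80%. This agrees with the text, which says that the comparison is matched.

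**2. Standard error of the by-arm test.**

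Let σ² be the total variance of the log cluster outcome and rho the within-pair correlation. The true variance of the difference in arm means over 6 pairs is 2σ²(1-rho)/6. The by-arm test estimates 2σ²/6. The ratio of standard errors is therefore 1/sqrt(1-rho). Critical values are t = 2.571 (5 df, paired) and t = 2.228 (10 df, by arm). The documents do not give rho, so a range is shown. Type I errors are simulated, 400,000 trials per setting.

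| rho | SE ratio | Type I error, by arm | Type I error, paired |
|---|---|---|---|
| -0.3 | 0.88 | 8.1% | 5.0% |
| 0 | 1.00 | 5.0% | 5.0% |
| 0.3 | 1.20 | 2.5% | 5.0% |
| 0.5 | 1.41 | 1.3% | 5.0% |
| 0.7 | 1.83 | 0.4% | 5.0% |

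**3. Power for a true ratio of 1.5.**

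This depends on what k = 0.2 measures, which the protocol does not say. Both readings were simulated with normal log cluster effects, leaving out the small sampling error from 400 respondents.

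*Reading A: 0.20 is the within-pair SD, and between-pair variation comes on top.*

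| Between-pair SD | Implied rho | Power by arm / paired | Mean CI half-width (log) by arm / paired |
|---|---|---|---|
| 0 | 0 | 88% / 80% | 0.25 / 0.28 |
| 0.10 | 0.20 | 83% / 80% | 0.28 / 0.28 |
| 0.20 | 0.50 | 65% / 80% | 0.35 / 0.28 |
| 0.30 | 0.69 | 41% / 80% | 0.45 / 0.28 |

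*Reading B: 0.20 is the total SD.*

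| rho | Power by arm / paired |
|---|---|
| 0 | 88% / 80% |
| 0.3 | 91% / 91% |
| 0.5 | 93% / 97% |

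The matched formula in step 1 uses k without any reduction for pairing, which fits Reading A. The protocol calls k simply the cluster coefficient of variation, which fits Reading B. Neither can be excluded.

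**The case against.** The strongest reply is that the article does not commit to an unpaired test. The analysis section never uses that word. It refers to methods suited to few clusters and says that the countries are analysed separately. The optional second-stage regression, with its degrees-of-freedom adjustment, could carry pair indicators, and would then give the same estimate, standard error and 5 df as a paired t-test. This stands in part: "unpaired" is the natural reading, not the stated word. But the regression is conditional and does not name pair, and the sentence that defines the test also governs Malawi, which has no pairs.

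A second reply is that the gain from pairing may be small. Matching within some pairs is loose: 53,249 against 24,078 people in pair 6, and 90 against 48 km in pair 4. Individual-level adjustment at the first stage may also remove some between-pair variation. With rho below about 0.3 the by-arm test is at least as powerful, because it has 10 df. This stands, and it is why the size of the effect is given as a range.

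Two stronger readings are tempting and are not supported. A reader might infer that the standard error is wrong whatever the data. It is correct at rho 0, and the documents do not report rho. A reader might also infer a risk of false positives. With the positive correlation that matching aims for, the error is conservative; inflation needs a negative rho, which nothing in the documents suggests. With equal cluster weights the point estimate on the log scale is the same either way.

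**Conclusion.** The point holds as a mismatch between design and analysis. Zambia is matched, randomised and powered in pairs, and its stated primary analysis does not use them.

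For positive rho the consequence is an interval that is too wide, by about 20% in standard error at rho 0.3 and 41% at rho 0.5, and a test run below its nominal 5%. The power consequence is not settled by the documents. It runs from an 8-point advantage for the by-arm test when pairs do not differ, through no difference at rho 0.3 with total SD 0.20, to a 15-point loss when between-pair SD 0.20 is added to within-pair SD 0.20. The 65% and 41% figures under Reading A should not be quoted as the expected power, because they hold only if k is within-pair variation.

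These results assume normal log cluster effects, equal cluster weights and two-sided alpha 0.05.

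**What to change.** In Trial analysis, state for Zambia that the primary test is a paired t-test on the six within-pair differences in log(observed/expected), with 5 df, giving the prevalence ratio, confidence interval and p-value. Equivalently, make pair a mandatory term in the second-stage regression: 12 clusters less an intercept, one arm term and five pair terms also leaves 5 df. Use the same approach for the unadjusted analysis and for the risk difference. Keep the two-sample t-test for Malawi.

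This is one or two sentences of text and no new data. The statistical price is 5 instead of 10 df, at most about 8 points of power (88% to 80%) if pairs do not differ.

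If the sponsor prefers to break the match, it should say so in advance, give the reason, and restate the Zambia power on an unmatched basis. Either way, the power section should say whether k = 0.2 is within-pair or total variation.

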### Economic analyses

#### Costing and cost effectiveness studies

The costing analysis will estimate the societal-level costs of community distribution of HIVST, both from the perspective of the health provider and the user, and will compare the costs of community HIVST distribution with standard HTS. The costing study will feed into estimates of cost-effectiveness, which will be projected on different time scales and population levels.

Full financial and economic costs from the providers’ perspective will be collected from PSI/SFH and from public health care facilities. User costs of accessing existing and new forms of HIV testing and linkage to care will be gathered using the extended baseline and endline questionnaires. Costing tools will be used in conjunction with service-related financial and activity reports in order to determine the unit costs of providing HTS and subsequent HIV care. We will also carry out detailed micro-costing, including time and motion studies, to clinics assigned to the intervention and control arms of the impact evaluation. This will help to identify instances of reduced crowding in ART clinics due to HIVST decentralisation. Gathered costing data will be used to conduct an economic evaluation, using decision-analytic modelling, to compare the costs of the different HIVST models to standard HTC models. Key outcomes will include the incremental cost per Disability Adjusted Life-Year (DALY) averted, which will allow the cost-effectiveness of HIVST and linkage to care models to be determined.

#### Discrete choice experiments

This study will administer two DCEs within baseline household surveys in Malawi and Zambia to inform HIVST implementation strategies. The first DCE will investigate preferences regarding delivery of HIVST relative to standard-of-care HTS, while the second DCE will evaluate preferences for linkage to onward HIV testing and care services [8]. We will sample approximately 500 participants for each DCE to allow for analysis of relative strength of preferences among the general population as well as among key sub-groups such as men and adolescents [23]. Participants will be randomly allocated to one of the two DCEs. We estimate HIV prevalence of 8.8% and 13% respectively in Malawi and Zambia [24, 25]. Respondents reporting HIV positive statuses were administered the linkage DCE. To elicit meaningful responses, the interviewer will present the HIV self-test kit to respondents and demonstrate the self-testing process at the beginning of the DCE.

Our analysis will include a simple multinomial logit and more complex choice models, such as mixed multinomial logit, latent class model and generalized multinomial logit model, to explore preference heterogeneity [26]. Socio-demographic characteristics and HIV-related experience will be explored to understand how they may influence respondents’ preferences.

### Qualitative research

Qualitative research related to the CRTs will include both exploratory and explanatory research as well as triangulation of findings across quantitative and qualitative methods. In the initial formative phase exploratory research will include an analysis of preferred self-test distribution models by age and sex to create an understanding of the concerns and preferences of various typical testers or ‘archetypes’. Results from preliminary analysis will be communicated to and discussed with implementers designing communications and marketing strategies as well as distribution models to shape delivery of self-tests. The formative research will also identify definitions and interpretations of harm among anticipated users, enabling us to better understand language around harm and coercion and to report harms using locally understood definitions. In-depth interviews with participants from the target populations will assess users’ cognitive understanding of instructions for use and ability to conduct tests, enabling us to develop support materials that optimise HIVST performance. Findings from these ‘cognitive interviews’ will also underpin the development of a training curriculum for distributors that addresses community concerns, demonstrates correct use of kits, and supports onward linkage. Finally, key informant interviews will be used to identify processes for and barriers to regulation of HIVST by national governments. As the study progresses we will undertake additional interviews with individuals and communities who have used HIVST to describe their experiences and help to probe behaviours around uptake, linkage, and coercive testing.

To facilitate cross-country qualitative research, we will establish an inter-country network of qualitative researchers (the qualitative research network) in STAR. This will allow for a robust analytical approach to the inter-country analysis of the qualitative findings that is interactive, collaborative and rooted in a strong understanding of the local contexts. Common data collection tools, sampling and coding frames will be developed iteratively through multiple rounds of joint discussion and analysis will thus feed into and be informed by the larger trial as an essential part of trustworthiness. We will use a framework approach to our qualitative analysis that will allow for both deductive and inductive themes to be captured and inform the larger trial at various stages as outlined above.

### Trial management

The trials will be overseen by an independent TAG, composed of up to six members who will be experts in research, health systems, policy, human resources and community health. The TAG meets semi-annually to review summaries of survey and monitoring and evaluation data, review any reports of severe adverse events or other social arms, and to assess the progress of these impact evaluations and other STAR research projects more generally. Both impact evaluations are short, pragmatic evaluations, and HIV self-testing is an established intervention. We do not expect substantial harms to result from the intervention, and will not establish a separate data safety monitoring board..

### Interim analysis and stopping rules

Interim survey data will be collected in intervention locations only to assess uptake of the intervention. These data will be collected between 4 and 6 months after the beginning of the intervention. Summaries of process and survey data will also be reviewed by the TAG. Frequencies of key process and outcome indicators will be distributed internally and to the donor. Because the intervention period will be brief and because we expect that there will be no substantial adverse impacts of the intervention, we will not establish a stopping rule for either study..

## Discussion

The STAR-Malawi and STAR-Zambia trials will provide rigorous evidence of whether community-based HIVST distribution is effective at increasing HIV testing uptake in rural and peri-urban communities in sub-Saharan Africa. Results from both CRTs and other STAR research will be used by local ministries to develop plans for self-testing in national HIV testing plans, and will be integrated into updated guidance for implementation of HIVST programmes by the WHO and other international organizations.

## Abbreviations

AE: Adverse events
ART: Anti-retroviral therapy
CBDA: Community-based distribution agents
CONSORT: Consolidated standards of reporting trials
CRT: Cluster randomized trial
DCE: Discrete choice experiments
DHS: Demographic and health survey
HIV: Human Immunodeficiecy Virus
HIVST: HIV self-testing
HTS: HIV testing services
IPV: Intimate partner violence
MWK: Malawi Kwacha
ODK: Open data kit
PHIV: People living with HIV
PSI: Population Services International
SAE: Severe adverse event
SFH: Society for Family Health
SOC: Standard of care
STAR: Self-Testing AfRica
TAG: Technical advisory group
USD: United States Dollars
VMMC: Voluntary Medical Male Circumcision
WHO: World Health Organization
ZAMRA: Zambian Medical Regulatory Authority
ZMW: Zambian Kwacha
